### Sample size

There is a growing body of research evaluating the effect of auricular acupressure for various diseases. However, there is still a lack of studies evaluating the effect of auricular acupressure on psoriasis. There is no previous study on which to base the sample size calculation. Thus, we used the primary outcome relapse rate to determine a sample size calculation. Based on the study of Menter et al. [42], the relapse rate of calcipotriol betamethasone ointment topical therapy after 4 weeks of treatment and 4 weeks of follow-up is 82%. We assume that the relapse rate of auricular acupressure therapy combined with calcipotriol betamethasone ointment topical therapy for psoriasis in week 12 is 20% less than topical therapy alone and that the relapse rate of calcipotriol betamethasone ointment topical therapy is 82%. On the basis of this hypothesis, and in order to compare the two groups for a significance level α = 0.05 and a power 1 – β = 0.80, we calculated the sample size by PASS statistics software (version 11.0.10; NCSS LLC., Utah, USA); 77 patients with psoriasis would have been required in each group to achieve 80% power to detect a difference between the group proportions of −0.2. The test statistic used is the two-sided *Z* test with pooled variance. The significance level of the test is targeted at 0.05. Considering 15% loss to follow-up, 90 patients are needed in each arm, totaling 180 patients in all.

### Data collection

Outcome measurements will be carried out and recorded using paper case report forms (CRF) and checked for each participant at every visit by a certificated clinical researcher. To promote patient enrolment, retention, and completion of follow-up, all the treatments and laboratory tests will be free. A 300 RMB gift will be sent to participants when they have completed the follow-up.

### Data management

Data managers will enter the information on the CRF into an electronic database using the double-entry method. There is no exclusive trial steering committee named in this trial. The integrity of CRF data in different centers will be monitored regularly by Guangdong International Clinical Research Center of Chinese Medicine (Guangzhou, China). As well as the safety data, and the critical efficacy outcomes will be assessed by the Data Monitoring Committee from GPHCM.

Patients will be pseudonymized by study identification numbers for participant confidentiality. Access to the CRF database will be limited to the study group and the coordinator.

### Statistical analysis

All analyses will be performed with PASS Statistics and SAS 9.2 software by a statistician who is blinded to the random allocation of groups. An intent-to-treat (ITT) basis statistical analysis with a 95% confidence interval will be performed using multiple imputations. The major imputation is multiple imputation by chained equations (MICE). The ITT analysis will include all patients who are randomized [43]. Safety analysis will be undertaken by analyzing the frequency of adverse events which are suspected as related to the treatment. Planned subgroup analyses include those based on the type of TCM syndromes and severity of psoriasis. The various parameters observed will be compared using a Chi-square test for noncontinuous variables (i.e., the primary outcome relapse rate) and *t* test and analysis of variance (ANOVA) for continuous variables. In order to distinguish the treatment effect and time effect, the repeated measures ANOVA change from baseline will be performed for the different time point assessments. Statistical significance is established at *P* < 0.05. No formal interim analysis is planned.

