## Methods/design

### Study design

This study is a two-parallel arm, assessor-blinded, randomized controlled trial. The trial will be conducted by Guangdong Provincial Hospital of Chinese Medicine (GPHCM) and performed at two clinical research centers in China (Guangdong Provincial Hospital of Chinese Medicine and Guangzhou Red Cross Hospital) in accordance with the Declaration of Helsinki and the Guidelines for Good Clinical Practice.

This study will select patients with blood stasis syndrome on a TCM diagnosis based on a TCM syndrome differentiation standard [29, 30]. Eligible participants will be stratified by age and sex and randomly allocated in a 1:1 ratio to one of the treatment arms (the auricular acupressure plus calcipotriol betamethasone ointment group or the control calcipotriol betamethasone ointment group) and receive treatment for 4 weeks, with 12 weeks of follow-up (Fig. 2). The Standard Protocol Items: Recommendations for Interventional Trials (SPIRIT) checklist is provided in Additional file 1.

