### Randomization

Eligible patients will be randomly assigned in a 1:1 ratio to one of the two groups (the treatment group who receive auricular acupressure plus calcipotriol betamethasone ointment or the control group who receive calcipotriol betamethasone ointment) at the second visit through central randomization. Equal randomization will be conducted using a computer-generated random allocation sequence through the stratified block randomization method of the SAS software (version 9.12; SAS Institute, Inc., Cary, NC, USA) with a block size of 4 by the Key Unit of Methodology in Clinical Research (KUMCR) of Guangdong Provincial Hospital of Chinese Medicine. Allocation concealment will be ensured since the randomization code will be released by the Interactive Web Response System for Chinese Medicine Trials (IWRS-CMT), which is a verified online randomization facility established by the KUMCR (http://www.gztcmgcp.net/sjxt /login.asp). Following this, the participants will be randomly allocated to the two different groups. The practitioners will be aware of the allocation arm according to the different medical procedures. However, the evaluation of participants and the analysis of the results will be performed by physician assessors and statisticians who are blinded to the group allocation [32].

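### Randomisation is stratified by age and sex, but the named tests use neither the strata nor the baseline value as a covariate: valid, conservative, and cheap to improve

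*Protocol article*

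**What the plan says.** **Design.** Under Study design: "Eligible participants will be stratified by age and sex and randomly allocated in a 1:1 ratio to one of the treatment arms". The Randomization section specifies stratified blocks "with a block size of 4".

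**Primary analysis.** Under Statistical analysis: "The various parameters observed will be compared using a Chi-square test for noncontinuous variables (i.e., the primary outcome relapse rate". The Sample size section rests on the matching unstratified test. "The test statistic used is the two-sided" Z test with pooled variance, planned "for a significance level α = 0.05 and a power 1 – β = 0.80", where "the relapse rate of calcipotriol betamethasone ointment topical therapy is 82" per cent and the difference to detect is 20 percentage points.

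**Continuous outcomes.** The plan names a t "test and analysis of variance (ANOVA) for continuous variables", and for repeated assessments "the repeated measures ANOVA change from baseline will be performed for the different time point assessments".

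The same section promises an intention-to-treat analysis with multiple imputation and a 95% confidence interval. Nowhere does the article name a stratified test, a regression adjustment, or a baseline value used as a covariate.

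**The concern.** Stratified blocks force the arms to be nearly balanced on age and sex, so differences in relapse between strata hardly enter the treatment contrast. An unstratified test still counts those differences as noise. Its standard error is then larger than the real sampling variability, and the test rejects less often than its nominal 5%.

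The continuous outcomes raise a separate point. Subtracting the baseline fixes its coefficient at 1, whereas ANCOVA estimates that coefficient. Unless the best coefficient happens to be 1, the change score is noisier than it need be.

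What is at stake is the width of the intervals for relapse, PASI, BSA, VAS and DLQI. The validity of the trial is not in question. Efficiency still matters, because the design has little slack: 90 per arm with 15% loss leaves 90 × 0.85 = 76.5 evaluable patients, against 77 required.

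**Working it through.** **1. The plan's own figure.** Inputs from the Sample size section: 82% vs 62%, two-sided α 0.05, power 0.80, pooled Z test. The mean proportion is 0.72.

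n = [1.960·√(2·0.72·0.28) + 0.8416·√(0.82·0.18 + 0.62·0.38)]² / 0.20² = (1.2445 + 0.5210)² / 0.04 = 77.9, so 78 per arm. At 77 per arm the power is 79.5%. The stated 77 reproduces within rounding. The pooled Z test is equivalent to the chi-square test without continuity correction, so sample size and analysis agree with each other.

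**2. Primary outcome.** The article gives neither the age cut-points nor the strength of age and sex as predictors of relapse, so both are assumed. The simulation used 154 evaluable patients, four equally likely age-by-sex strata, blocks of 4, and 40,000 runs per setting. Stratum log-odds were offset by ±0.447 and ±1.342 times an assumed SD. The unstratified chi-square was compared with the Cochran-Mantel-Haenszel (CMH) test. Power and standard errors are at 82% vs 62%; type I error is at 72% in both arms.

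| Assumed SD | Control relapse by stratum | Power: chi-square / CMH | Reported SE ÷ true SE | Type I error: chi-square / CMH |
|---|---|---|---|---|
| 0 | 82% in all | 80.0% / 79.8% | 0.99 | 5.0% / 4.9% |
| 0.3 | 76, 80, 84, 88% | 80.2% / 80.5% | 1.00 | 4.8% / 5.0% |
| 0.5 | 72, 80, 86, 91% | 80.4% / 81.5% | 1.02 | 4.5% / 4.9% |
| 0.75 | 66, 79, 88, 94% | 81.1% / 83.4% | 1.04 | 3.9% / 4.9% |
| 1.0 | 62, 80, 91, 96% | 82.0% / 86.2% | 1.08 | 3.2% / 4.9% |

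The two estimates themselves are about equally precise. At SD 1.0 the true SE is 0.0646 unadjusted and 0.0645 stratified, while the unadjusted analysis reports 0.0701. The stratified blocks have already delivered the balance; the unstratified analysis does not take credit for it.

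**3. Continuous outcomes, one follow-up visit.** Let s0 and s1 be the baseline and follow-up SDs and r their correlation. Per patient:

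- change score variance: s0² + s1² − 2·r·s0·s1
- ANCOVA variance (large samples): s1²·(1 − r²)
- difference: (s0 − r·s1)², which is never negative

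The direction therefore holds for any pair of SDs. With s0 = s1, the ratio ANCOVA ÷ change is (1 − r²) / [2(1 − r)] = (1 + r)/2.

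| Assumed r | Variance ratio | Change-score SE ÷ ANCOVA SE |
|---|---|---|
| 0.3 | 0.65 | 1.24 |
| 0.5 | 0.75 | 1.15 |
| 0.7 | 0.85 | 1.08 |

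With unequal SDs and k = s0/s1, the ratio is (1 − r²) / (1 + k² − 2rk). At r = 0.5 it is 0.75/0.76 = 0.99 for k = 0.6 and 0.75/1.75 = 0.43 for k = 1.5. The size of the gain thus depends on the SD ratio as well as on r, and the article gives neither.

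**The case against.** The strongest reply is that the plan is coherent and safe as written. The test that sized the trial is the test that will be run. In every simulated setting its power was at least 80% and its type I error was not inflated. Nothing in the article says that age or sex predicts relapse. The determinants named in the Discussion, for cyclosporine, are disease severity, dose required and extent of clearing. At an assumed SD of 0.3 the standard error is less than 1% too wide, and at 0.5 about 1.7%. A separate analysis plan might also add adjustment. All of this stands, and it limits the size of the point. It does not remove it: the article itself names the primary test and the continuous-outcome tests, and a stratified analysis costs essentially nothing even when the strata carry no information.

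A reader might infer more than the article supports:

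- **That multiple imputation rules out the chi-square.** It does not. Special rules exist for pooling chi-square statistics. They do not in themselves supply the promised confidence interval, which a pooled risk difference does.
- **That regression to the mean biases the change scores.** With a concurrent randomised control it is expected equally in both arms. What remains is imprecision and sensitivity to chance baseline imbalance.
- **That baseline PASI is used only by subtraction.** It also enters the definitions of relapse, PASI-50 and rebound, and disease severity is a planned subgroup.
- **That the continuous-outcome gain carries over to the primary outcome.** Ratios of 0.65 to 0.85 correspond to 1/0.85 = 1.18 to 1/0.65 = 1.54 times as many patients, but only for secondary outcomes and only with equal variances.

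**Conclusion.** The point holds as one of efficiency. The analysis leaves out the stratification factors and the baseline covariate, although both are available. The named tests remain valid, their error is in the conservative direction, and the stated sample size is unaffected.

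For relapse the loss is conditional and probably small: 0 to 8% on the reported standard error, with type I error between 5.0% and 3.2%, over assumed stratum log-odds SDs of 0 to 1.0. The upper end needs control relapse to run from 62% to 96% across strata, which nothing in the article supports. For continuous outcomes ANCOVA is, in large samples, never less precise than the change score. The variance ratio of 0.65 to 0.85 rests on equal variances and an assumed correlation of 0.3 to 0.7, and it moves in either direction when the SDs differ. It would be wrong to conclude that the trial is underpowered or that its primary test is invalid.

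**What to change.** **Relapse.** Make the primary analysis a risk difference stratified by or adjusted for age stratum and sex, for example a Mantel-Haenszel risk difference or a model-based one. Baseline PASI is an optional further covariate. Estimate it with its standard error in each imputed data set and pool by Rubin's rules, which gives the promised 95% confidence interval. Keep the unadjusted chi-square as a sensitivity analysis.

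**PASI, BSA, VAS and DLQI.** Use ANCOVA, or a repeated-measures model, with the baseline value, age stratum and sex as covariates. Centre is not a stated stratum, so adjusting for it is optional.

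**Cost.** A change of wording and slightly more analysis work. No new data are needed: age and sex are used at randomisation, and the planned change scores already require the baseline values. The change should be dated and made before unblinding. The article states that the statistician is blinded and that no formal interim analysis is planned. If a separate analysis plan already specifies adjustment, the two documents need only be aligned.

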#### Secondary outcome measurements

Secondary outcome measures include the time to relapse, rebound rate, time to new onset, PASI improvement rate, BSA affected, a visual analog scale (VAS), and Dermatology Life Quality Index (DLQI). Time to relapse is defined as the time it takes to lose 50% of the improvement obtained from treatment (Table 1). Time to new onset is the PASI score improvement achieved (PASI-50) for the first time, but a failure to keep the PASI-50 improvement all through the treatment period. Rebound is defined as a PASI score of 125% of that at baseline, or the occurrence of new generalized pustular, erythrodermic, or more inflammatory psoriasis occurring [41]. The VAS and BSA will be assessed every week during the first 4 weeks and every 2 weeks in the follow-up period. The DLQI will be self-assessed by patients every 4 weeks throughout the trial. Laboratory reports will be also monitored until the last visit. TCM syndrome is one of the assessments which will be recorded before and after the auricular acupressure, as well as at the end of the follow-up period (Table 2).

**Table 1 Tab1:** Summary of measurement

Outcome	Measurement tool	Details
Primary outcome		
Relapse rate	Psoriasis Area and Severity Index (PASI) score	Relapse defined as losing 50% of the improvement obtained from treatment once the treatment is stopped
Secondary outcome		
Time to relapse	PASI score	Time domain between achieving at least 50% reduction in PASI score and losing 50% of the improvement obtained from treatment once the treatment is stopped.
Time to new onset	PASI score	Time domain between lesion clearing and recurrence
Rebound rate	PASI score	Rebound defined as a severe and sudden change in the severity of psoriasis that is significantly worse than before the treatment was initiated
PASI improvement rate	PASI score	PASI score is a tool used to measure the severity and extent of psoriasis. It takes a few minutes and experience to calculate it accurately. A representative area of psoriasis is selected for each body region. The intensity of redness, thickness, and scaling of the psoriasis is assessed as none (0), mild (1), moderate (2), severe (3), or very severe (4)
VAS	Visual analog scale (VAS)	VAS is the most common pain scale for quantification of endometriosis-related pain. We use VAS to evaluate the feeling of pruritus in participants during the treatment period

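### The only test rule for continuous outcomes is a t test or ANOVA, with no censored-data method for time to relapse or time to new onset, and time to new onset has two incompatible definitions

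*Protocol article*

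**What the plan says.** The protocol article lists time to relapse and time to new onset among its secondary outcomes.

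- **Time to relapse.** Secondary outcome measurements: "Time to relapse is defined as the time it takes to lose 50% of the improvement obtained from treatment". Table 1 adds a starting point, a PASI reduction of at least 50%, and ties the loss to stopping treatment.
- **Time to new onset, text.** "Time to new onset is the PASI score improvement achieved (PASI-50) for the first time", followed by failure to hold that improvement through the treatment period.
- **Time to new onset, Table 1.** "Time domain between lesion clearing and recurrence".
- **Analysis.** The Statistical analysis section sets one rule for the parameters observed: chi-square for noncontinuous variables and a t "test and analysis of variance (ANOVA) for continuous variables", plus repeated measures ANOVA of change from baseline. The analysis is by intention to treat in all randomised patients, with multiple imputation by chained equations (MICE).
- **Expected rates.** Sample size assumes that "the relapse rate of calcipotriol betamethasone ointment topical therapy is 82"%, and that the combined arm is 20 points lower at week 12.

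The article names no Kaplan-Meier, log-rank, Cox or interval-censored method and gives no censoring rule.

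**The concern.** A duration is a continuous variable, so the rule as written sends both time outcomes to a t test or ANOVA. Those tests need an observed value for every patient. A patient who has not relapsed when follow-up ends has only a lower bound. On the planning rates there are about twice as many such patients in the combined arm as in the control arm, so the way they are handled bears directly on the treatment comparison. The article does not say which handling applies.

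The two definitions of time to new onset are a separate problem that no choice of test can repair. Two analysts following the text and the table would study different patients and different events.

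Time to relapse is the first-listed secondary outcome and bears on the stated primary aim, control of recurrence.

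**Working it through.** **1. The plan's own figure.** Inputs from Sample size: 82% and 62% relapse, "The test statistic used is the two-sided" Z test with pooled variance, "The significance level of the test is targeted at 0.05", and 77 patients "in each group to achieve 80% power to detect a difference between the group proportions".

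n per arm = [1.960·√(2·0.72·0.28) + 0.842·√(0.82·0.18 + 0.62·0.38)]² / 0.20² = (1.2445 + 0.5210)² / 0.04 = 77.9, so 78. The plan states 77, at which power is 79.5%. Then 77/0.85 = 90.6 against the stated 90. Both agree closely, and they confirm that 20% means percentage points: a relative reduction (65.6%) would need 112 per arm.

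**2. Patients without a relapse time.** Control: 1 − 0.82 = 18%, or 77 × 0.18 ≈ 14. Combined: 1 − 0.62 = 38%, or 77 × 0.38 ≈ 29. Loss to follow-up comes on top.

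**3. What each handling would do.** Assumptions, not in the documents: exponential relapse times, a window T of 12 weeks, all 77 per arm at risk, and no dropout except where stated.

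- Rate λ = −ln(1 − p)/T. Hazard ratio = ln 0.38 / ln 0.18 = 0.56.
- Log-rank, Schoenfeld: events = 77 × (0.82 + 0.62) = 110.9; power = Φ(√(110.9/4) × |ln 0.564| − 1.96) = Φ(1.05) = 85%.
- Mean among relapsers only = 1/λ − T(1 − p)/p. Control: 7.00 − 2.63 = 4.36 weeks. Combined: 12.40 − 7.35 = 5.05 weeks. Difference about 0.7 weeks.
- Restricted mean over 12 weeks = p/λ. Control: 5.74. Combined: 7.69. Difference 1.95 weeks. With times rounded up to two-weekly visits: 6.60 and 8.33, difference 1.73 weeks.

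Simulated power:

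| Analysis | Exact times (5,000 trials) | Two-weekly visits (1,500 trials) |
|---|---|---|
| t test, relapsers only | 18.6% | 16.8% |
| t test, last visit taken as event | 81.5% | 77.5% |
| Log-rank | 86.4% | 85.9% |

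The last-visit t test therefore loses 4.9 points with exact times and 8.4 points with two-weekly visits.

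**4. Type I error.** With no true effect and a common 12-week cut-off, the last-visit t test rejects in 5.1% of trials and log-rank in 5.6%. With no true effect, 90 per arm and an assumed dropout of 5% in one arm and 25% in the other (15% overall), the figures are 10.5% and 5.4%.

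**5. Imputation.** This was not simulated. A patient seen to be relapse-free at the end of follow-up is not missing a value; the time is known to exceed the follow-up. Standard imputation of a continuous time learns only from relapses observed within follow-up, so it tends to assign these patients an early relapse that they did not have.

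**6. Time to new onset, side by side.**

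| | Text | Table 1 |
|---|---|---|
| Start | First PASI-50 | Lesion clearing |
| Event | PASI-50 not kept | Recurrence |
| Window | Treatment period | Not limited to treatment |
| Patients | All who reach PASI-50 | Only those who clear |

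A patient who reaches PASI-50 without clearing counts under the text and not under Table 1.

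**The case against.** The Statistical analysis section does not name either time outcome. Its sentence is generic, the article condenses a longer document, and a statistical analysis plan could specify a survival method. That stands in part: the article does not prove that a t test will be run on relapse times. But its sentence covers the parameters observed without exception, so it sets an unsuitable default, and a later plan using log-rank would have to depart from it.

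Three stronger readings are tempting and are not supported.

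- *Most of the power is lost.* This is true only if non-relapsers are dropped. The article does not say so, and its intention-to-treat rule includes all randomised patients. If everyone is kept with the last visit as the event, the loss is modest and, with a common cut-off, the test holds its level.
- *A true difference of 5.4 weeks is being hidden.* That figure is the gap between unrestricted exponential means (12.4 − 7.0), which extrapolates beyond follow-up. No method recovers it from 12 weeks of data. The restricted-mean difference is 1.95 weeks, or 1.73 on two-weekly visits, and a last-visit t test showing about 1.7 weeks is estimating that quantity.
- *Both outcomes should run from randomisation.* Neither definition of time to new onset starts there, so this would add a third origin instead of reconciling the two.

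The calculations also treat every patient as at risk, whereas Table 1 starts time to relapse at a 50% PASI reduction, so only responders enter. No figure here concerns time to new onset. The conflict between its two definitions has no counter-argument in the text.

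**Conclusion.** The point holds, in two parts. First, the article's only rule for continuous outcomes does not suit its two time outcomes, and it gives no censoring rule although its own rates leave about 18% and 38% of patients without a relapse time. The consequence ranges from mild (about 5 to 9 points of power, with level held under a common cut-off) to severe (a difference of about 0.7 weeks and power under 20% if only relapsers are analysed), with a type I error near 10% in the assumed case of uneven dropout. These sizes rest on exponential times, a 12-week window and full risk sets. Second, time to new onset is defined in two ways that cannot both be applied; this follows from the text alone.

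A reader might infer that the trial's main result is at risk. It is not: the primary relapse rate, its chi-square test and the sample size of 180 stand. Nor do the documents show that the secondary results would necessarily be wrong; they leave that to an unstated choice.

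**What to change.** - In Statistical analysis, exempt both time outcomes from the t test/ANOVA rule. Analyse them with Kaplan-Meier curves, a log-rank test and a Cox hazard ratio, or an interval-censored equivalent where the event is dated only by visits. Censor event-free patients at their last PASI assessment, and state that relapse times are not imputed for patients still relapse-free at the end of follow-up.
- Reconcile the text and Table 1 into one definition of time to new onset.
- For each time outcome, state one time origin and one risk set, the same in both arms, including how patients who never reach the starting state are counted.

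The cost is a few sentences and one corrected definition. No new data are needed and the sample size does not change. The article reports 154 of 180 patients recruited and no planned interim analysis, so the change can be recorded before the allocation is unblinded.
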